#### Safety assessment

2.10.2

Adverse events (AEs) will be reported and recorded in detail during the entire study. The following will be used to assess safety: vital signs, CBC, chemistry, and urine tests, and electrocardiography. Safety-related variables will be analyzed using the intention to treat (ITT) data set. Comparisons between the ratio of the number of participants who experienced 1 or more adverse events to the total number in that group or subgroup will be performed using a chi-square analysis or Fisher exact test. The statistical significance of the changes between subgroups/groups will be tested using the 2-sample *t* test or the Mann–Whitney test. In addition, the statistical significance of changes within each group will be tested using the paired *t* test or Wilcoxon singed-rank test. Electrocardiography results and some urine-test results will be classified as normal and abnormal according to clinical significance, and comparisons within groups will be analyzed using the McNemar test.

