Some patients seek to receive alternative safe and effective therapies such as herbal medicines for the treatment of cancer-related anorexia.^[11]^ Yukgunja-tang (YGJT), also known as Rikkunshito in Japan and Liu-Jun-Zi-Tang in China, is a traditional herbal medicine extensively prescribed in East Asian countries for the treatment of patients with various gastrointestinal syndromes, such as anorexia, nausea, dyspepsia, gastritis, and gastroesophageal reflux disease.^[12–18]^ A number of experimental studies have shown that YGJT may be effective in treating cisplatin-induced anorexia.^[19–21]^ However, additional clinical evidence for YGJT being a practical approach to treating such patients is needed. Therefore, we designed a randomized, controlled clinical trial to examine the efficacy and the safety of using YGJT to treat anorexia in patients suffering from cancer. Also, this pilot study will be performed to gather more evidence in support of recommending YGJT as a standard treatment for patients with cancer-related anorexia.

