### Study design

2.1

This study is a double-blind, randomized, controlled trial that aims to examine the efficacy and the safety of using YGJT to treat patients with cancer-related anorexia. All patients fulfilling the eligibility criteria will be selected. The enrolled participants will be randomly allocated to 2 groups: The control group will receive nutrition counseling, and the YGJT group will receive nutrition counseling and be administered YGJT. Figure 1 shows the schematic flow of this YGJT clinical trial.

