### Withdrawal criteria

2.5

Participants who meet the withdrawal criteria will be dropped from the trial. Participants who withdraw or are dropped after randomization will be followed for outcomes. The withdrawal criteria include the use of any forbidden medication or treatment during the trial that could affect the study result, the participant's withdrawal of consent, the occurrence of a serious adverse event, the detection of eligibility violations, the occurrence of other significant protocol violations during the trial, and the investigator's decision to terminate the process for the sake of the participant's health.

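### ECG and categorical urine results are tested only within each arm, so they have no suitable comparison with control; assigning safety to the ITT set is a smaller, conditional weakness

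*Protocol article*

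**What the plan says.** All of the safety analysis is in section 2.10.2 (Safety assessment) of the protocol article.

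- Analysis set: "Safety-related variables will be analyzed using the intention to treat (ITT) data set".
- Participants with at least one adverse event: the proportion "in that group or subgroup will be performed using a chi-square analysis or Fisher exact test". This is a comparison between arms.
- Changes in safety variables: "The statistical significance of the changes between subgroups/groups will be tested using the 2-sample" t test or the Mann–Whitney test. This is also between arms. Within-arm tests are then added: "In addition, the statistical significance of changes within each group will be tested using the paired" t test or the signed-rank test.
- ECG and some of the urine tests: each result is reduced to normal or abnormal, and "comparisons within groups will be analyzed using the McNemar test". No other test is named for these items.

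Two other places bear on the point. Section 2.1 sets the contrast: "The control group will receive nutrition counseling, and the YGJT group will receive nutrition counseling and be administered YGJT". Section 2.5 says of those who leave: "Participants who withdraw or are dropped after randomization will be followed for outcomes".

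**The concern.** Safety is a stated aim alongside efficacy, and a randomised control arm lets a change over four weeks be attributed to YGJT rather than to the cancer or its treatment. McNemar's test asks only whether, inside one arm, moves from normal to abnormal outnumber moves the other way. It makes no use of the control arm. In this population some ECG and urine results may well worsen without YGJT. A positive test in the YGJT arm could then be read as harm, and a negative one as reassurance, when neither says how YGJT compares with counselling alone. Setting one arm's p-value beside the other's does not repair this.

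The secondary concern is the analysis set. ITT classifies by assignment. A participant assigned to YGJT who never takes it adds to the YGJT denominator without having been exposed, which tends to pull a true excess of events towards zero. For safety that is the less cautious direction.

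**Working it through.** **The plan's own figure.** The article gives no numerical target for safety. Its only design figure is the sample size in section 2.6, which reproduces: 2 × 1.2346 × (2.0211 + 0.8507)² = 20.36, rounded up to 21; 21 × 1.2 = 25.2, rounded up to 26 per arm. The illustrations below use 26 per arm.

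**Within-arm against between-arm tests.** Assume that all 26 in each arm are normal at baseline, all are assessed again, and none moves from abnormal to normal. With *b* new abnormalities, the exact two-sided McNemar p-value is 2 × 0.5^b.

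| | New abnormalities | Exact McNemar p |
|---|---|---|
| One arm | 6 of 26 | 2 × 0.5⁶ = 0.031 |
| Other arm | 5 of 26 | 2 × 0.5⁵ = 0.063 |

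- Between arms, Fisher's exact test on 6/26 against 5/26 gives p = 1.00.
- The risk difference is 6/26 − 5/26 = 0.231 − 0.192 = 0.038.
- Its standard error is √(0.231 × 0.769/26 + 0.192 × 0.808/26) = 0.113.
- The approximate 95% CI is 0.038 ± 1.96 × 0.113, or −18 to +26 percentage points.

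The plan's tests would therefore put the two arms on opposite sides of 0.05 when they differ by one participant.

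**How often this could happen.** Suppose both arms truly have a 20% risk of a new abnormality (an assumption) and none reverses. An arm reaches p < 0.05 with 6 or more of 26, which has probability 0.4225. The chance that YGJT reaches it and control does not is 0.4225 × (1 − 0.4225) = 0.244, or about 24%, with no difference between treatments.

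**What the between-arm test can show.** 6 of 26 against 0 of 26 gives Fisher p = 0.023, and 5 against 0 gives p = 0.051. The test is weak at this size, so the interval matters more than the p-value.

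**The ITT set.** The article gives neither an adverse-event rate nor a number never dosed. Assume 30% on YGJT and 10% on control, with *k* of 26 never dosed and at the control rate. The ITT risk difference is then 0.20 × (26 − k)/26.

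| k never dosed | ITT risk difference (points) | Relative loss |
|---|---|---|
| 0 | 20.0 | none |
| 1 | 19.2 | 4% |
| 2 | 18.5 | 8% |
| 5 | 16.2 | 19% |

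The relative loss is k/26 whatever the two event rates are, provided the undosed have the control rate. Power is a poor gauge here because Fisher's test is discrete. In this example the calculated power is 0.32 with 26 dosed against 26 controls, yet 0.40 with 25 against 26.

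**The case against.** A reader might infer from section 2.10.2 that harm from YGJT is never compared with control. The text does not support that. Adverse-event incidence and changes in other safety variables are both tested between groups, with the within-arm tests as additions. The gap is confined to ECG and some, not all, urine results. One might also say that the between-group sentence on changes covers those items. But t and Mann–Whitney tests do not suit a normal/abnormal result, the chi-square or Fisher test is stated for adverse events, and the dichotomised items get a sentence of their own that names only McNemar. A clinically important ECG finding might also be counted as an adverse event, but the article does not say so.

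On the analysis set, the objections carry more weight.

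- The article does not define ITT, and a fuller plan may do so.
- No rate of never-dosed participants is given, and with none the two sets agree for the YGJT arm.
- A reader might argue that controls will obtain YGJT, since it is "a traditional herbal medicine extensively prescribed in East Asian countries". That says nothing about use by controls in this trial. Section 2.8 prohibits other anorexia treatment, section 2.5 makes forbidden medication a ground for withdrawal, and section 2.11 monitors compliance. Contamination is not relied on here.
- Dilution is not certain in every data set, because an undosed participant can have disease-related events that raise the YGJT count.
- With 2 undosed, it is tempting to say that the YGJT event rate itself falls by the factor 24/26 = 0.92. That holds only if the undosed have no events. At the control rate it becomes (24 × 0.30 + 2 × 0.10)/26 = 28.5%, a factor of 0.95.

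The article also names no analysis set for efficacy. An article commonly leaves that to the full protocol or analysis plan, so it is no fault here.

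**Conclusion.** The main point stands in its narrow form. For ECG and the dichotomised urine results, the plan fixes a within-arm test and names no suitable comparison with control. This does not depend on any assumed rate. The numerical illustrations do: they assume 26 per arm, all normal at baseline and none reversing, and the 24% figure also assumes a 20% risk in both arms.

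The ITT point is secondary and conditional. The loss is about 4% to 8% of the risk difference with 1 or 2 of 26 never dosed, and nil if everyone is dosed. On its own it would be a minor wording matter. The trial is an exploratory pilot with little power for safety, so what is at stake is an interpretable controlled estimate to carry into later trials rather than a formal decision.

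**What to change.** 1. For ECG and each categorical urine result, compare between arms the proportion newly abnormal at follow-up among those normal at baseline. Report the risk difference with a 95% CI and Fisher's exact test. Show the full baseline-by-follow-up shift table for each arm, and keep McNemar as descriptive.
2. Analyse safety by treatment actually received, with ITT as a sensitivity analysis. Define the rule before the data are examined and report how many participants assigned to YGJT were never dosed.

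The cost is wording in the analysis plan and a few table columns. All the data are already to be collected. The small downside of the second change is that groups formed by treatment received depart slightly from the randomised groups, which is why the ITT result should stay beside it.

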### Inclusion criteria

2.3

Participants meeting the following criteria will be included: Patients who have a histologically or cytologically confirmed solid tumor; individuals who are suffering from anorexia; men and women aged 20 to 80 years who can write, read, and understand; score on the Visual Analog Scale (VAS) for anorexia ≥ 40/100 mm; neutrophils ≥ 1500/μL, platelets ≥ 100,000/μL; total bilirubin of the maximum normal level or less (1.2 mg/dL); alanine aminotransferase (ALT) and aspartate aminotransferase (AST) levels lower than twice the upper limit for normal (35/45U/ℓ); creatinine level lower than 1.5 times the upper limit for normal (1.09 mg/dL); patients who provide written informed consent for participation in the trial.

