### Sample size

2.6

This study is an exploratory trial conducted before a confirmatory trial to establish the validity of using YGJT to treat patients with cancer who are suffering from anorexia. The efficacy of YGJT will be examined in order to provide information that will lead to a better design for a future clinical trial. Considering a dropout rate of 20%, we calculated that a total of 52 subjects, 26 per group, should be enrolled in this study. The sample size was set using an effective size of 0.9, which is the ratio of the standard deviation of each group from the mean difference of outcomes between the YGJT group and the control group at a significance level of 5% and a power of 80%. The formula for estimating the sample size is as follows:  

where n is the approximate sample sizes required per group, *t*_*α,v*_ is the 97.5 percentile score of the *t* distribution with *v* degrees of freedom, and *t*_*β*(1),*v*_ is the 80 percentile score of the *t* distribution with *v* degrees of freedom. If *v* = 40, n′ ≥ 2 × 1.2346 × (2.0211 + 0.8507)^2^ = 20.3632 (21). For a dropout rate of 20%, the sample size for each group is given by n = 21 × 1.2 = 25.2 (26). Therefore, a total of 52 subjects, 26 in each of the 2 groups, will be enrolled in this study.

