#### Subgroup analysis

2.10.3

The efficacy of YGJT between subgroups will be evaluated as follows: comparison of the YGJT efficacy for each of the subgroups in the YGJT group with that of the corresponding subgroup in the control group and comparison of the YGJT efficacy among the 3 subgroups of the YGJT group. The statistical significance of any differences between the YGJT group and the control group, among the 3 subgroups, will be analyzed using a generalized linear model with either the Wilcoxson rank sum test or the Kkruskal–Wallis test. All tests will be 2-sided tests, and the significance level will be 0.05.

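### For blood count and chemistry values the safety section sets only tests of change, which respond poorly when a few patients are affected; per-patient abnormality counts by arm should be added

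*Protocol article*

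**What the plan says.** Section 2.10.2 (Safety assessment) of the protocol article names vital signs, blood count, chemistry, urine tests and ECG as the safety measures and analyses them in the intention-to-treat set. It then sets out three kinds of analysis.

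- **Adverse events:** the proportion of patients with at least one event, compared by chi-square or Fisher's exact test, by group or subgroup.
- **Changes:** "The statistical significance of the changes between subgroups/groups will be tested using the 2-sample *t* test or the Mann–Whitney test", with paired t or signed-rank tests within each group in addition.
- **Classification:** "Electrocardiography results and some urine-test results will be classified as normal and abnormal according to clinical significance", compared within groups by the McNemar test.

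Blood count and chemistry are not in the third list, so for their values only the second kind applies. Section 2.9.4 defines three subgroups. The level is stated in section 2.10.3: "All tests will be 2-sided tests, and the significance level will be 0.05". No text calls the safety p-values descriptive or adjusts them. Section 2.9.3 has all safety variables recorded at every visit. Section 2.3 gives entry limits for neutrophils, platelets, bilirubin, ALT, AST and creatinine.

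**The concern.** Laboratory harm from a medicine usually shows as large shifts in a few patients and little change in the rest. A test of the mean or of ranks is poorly suited to that pattern. In the t test the extreme values inflate the standard deviation along with the mean. In a rank test each affected patient counts only as one of the top ranks, however large the rise.

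The same tests, repeated over many variables and in subgroups, will also produce some significant results by chance.

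Safety is a stated aim alongside efficacy, and the trial is meant to inform later trials. What is at stake is a report that presents a non-significant ALT or platelet comparison as reassurance although several YGJT patients had marked abnormalities, next to a few significant mean changes that are noise.

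**Working it through.** **Inputs from the document.** "Therefore, a total of 52 subjects, 26 in each of the 2 groups, will be enrolled in this study" (section 2.6). This reproduces: 2 × (1/0.9²) × (2.0211 + 0.8507)² = 2 × 1.2346 × 8.2472 = 20.36, rounded up to 21; 21 × 1.2 = 25.2, rounded up to 26. Level 0.05 two-sided; three subgroups. The article states no detection or error figure for the safety analysis, so there is none to reproduce.

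**Assumptions (not in the document).** SD of ALT change 8 or 20 U/L; affected patients rise by 50–100, 90–130 or 100–300 U/L; 15 to 40 continuous safety variables.

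**Step 1: ceiling of the t statistic.** Suppose k of n YGJT patients rise by the same amount x, and x is so large that other variation is negligible.

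- Mean difference = kx/n.
- YGJT variance = x²·k(n−k)/[n(n−1)]; control variance ≈ 0.
- Hence t = √[k(n−1)/(n−k)], in which x cancels.

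With n = 26:

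| k | t |
|---|---|
| 1 | √(25/25) = 1.00 |
| 2 | √(50/24) = 1.44 |
| 3 | √(75/23) = 1.81 |
| 4 | √(100/22) = 2.13 |
| 5 | √(125/21) = 2.44 |

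The critical value on 50 degrees of freedom is 2.01. In this limit, three patients do not reach significance however large the rise. Four are needed.

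**Step 2: simulation.** 26 per arm; normal changes with mean 0; k YGJT values replaced by uniform rises; 10,000 runs. Percentage of runs with p<0.05, as t / Mann–Whitney:

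| SD, rise (U/L) | k=1 | k=2 | k=3 | k=4 | k=5 |
|---|---|---|---|---|---|
| 8, 50–100 | 2.5 / 4.7 | 6.4 / 5.7 | 19 / 9.0 | 44 / 13 | 75 / 18 |
| 8, 90–130 | 1.1 / 4.5 | 3.8 / 6.1 | 18 / 9.3 | 55 / 14 | 92 / 18 |
| 8, 100–300 | 0.2 / 4.9 | 0.4 / 6.4 | 6.1 / 8.9 | 56 / 13 | 98 / 18 |
| 20, 50–100 | 5.1 / 4.9 | 8.3 / 5.8 | 15 / 8.5 | 25 / 12 | 38 / 18 |
| 20, 90–130 | 4.6 / 4.7 | 9.1 / 6.2 | 18 / 8.2 | 34 / 13 | 55 / 19 |
| 20, 100–300 | 2.7 / 5.2 | 5.9 / 6.1 | 17 / 8.8 | 41 / 12 | 74 / 18 |

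With nobody affected, both tests give about 5%. One or two affected patients are therefore barely distinguishable from none, and with the t test they can lower the rate below 5%. A run with 21 per arm and fixed rises of 5 or 12.5 SD gave similar results at k=3 (t 18–19%, Mann–Whitney 9.7%).

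**Step 3: number of tests.** Read literally, the section gives between-group tests in the whole sample and in three subgroups (4), and paired tests within each arm (2), so 6 per variable. If all null hypotheses are true, expected chance results = variables × 6 × 0.05:

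- 15 variables: 90 tests, 4.5 results.
- 25 variables: 150 tests, 7.5 results.
- 40 variables: 240 tests, 12 results.

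These expectations do not require independence. Simulating 20 variables with the four between-group tests only (80 tests) gave about 4 chance results on average. The chance of at least one was 97%, 94% and 85% at correlations of 0, 0.3 and 0.5 between variables.

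**Step 4: what counts would add.** For 3 of 26 against 0 of 26, Fisher's exact p = 2 × C(26,3)/C(52,3) = 2 × 2600/22100 = 0.24. For 2, 4 and 5 against 0 it is 0.49, 0.11 and 0.051. The exact 95% interval for 3/26 (11.5%) is 2.4% to 30.2%, and for 0/26 it is 0% to 13.2%. Counts show the affected patients; they do not make the comparison significant.

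**The case against.** **Adverse events.** A reader might infer that marked laboratory toxicity would go undetected. The article does not support that. Adverse events are recorded in detail throughout, and nothing excludes laboratory abnormalities from them, so a rise of 100 U/L or more may well be reported as an event and enter the per-patient comparison. This stands. But no text ties laboratory limits to adverse events, and a count of patients with any event would not show a liver or blood signal separately.

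**Larger numbers affected.** The t test does respond at four or five patients (25–56% and 38–98% in the table), and at five it can do better than Fisher's test. This stands too. The case for counts is descriptive, not one of power.

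**Number of tests.** A reader might count within-arm paired tests in every subgroup, making 12 tests per variable, or 300 tests and 15 chance results for 25 variables. The section mentions subgroups for the between-group tests and places the paired tests within each group, so six per variable is the literal reading.

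**Article format and pilot status.** Shift tables and listings are often left to the full protocol or analysis plan, and unadjusted safety p-values are common in a pilot. Their absence alone would be no finding. Here, however, the article itself chooses which results are classified and gives blood count and chemistry only tests of change.

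**Conclusion.** The point holds as a limited one. For blood count and chemistry values, section 2.10.2 sets only tests of change, beside an any-event comparison that does not isolate laboratory toxicity. With 26 per arm these tests stay near their false-positive rate when one or two YGJT patients are affected. With three affected (3/26 = 12% of the arm) they miss in about 81 to 94% of runs (t) or about 91 to 92% (Mann–Whitney). The same wording yields roughly 4.5 to 12 chance results.

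The detection figures rest on the assumed SDs and rises, though the ceiling in step 1 does not depend on the size of the rise once it is large. The count of chance results rests on an assumed 15 to 40 variables and the literal six tests each. It does not follow that the tests of change are invalid or that their p-values must be dropped. The conclusion is that they cannot carry the laboratory safety assessment. This is a worthwhile, cheap improvement and not a flaw that threatens the trial.

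**What to change.** In section 2.10.2, add for each blood count and chemistry variable:

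1. Classify every post-baseline value against the laboratory's reference limits and, for the six analytes in section 2.3, against the entry limit. For neutrophils and platelets section 2.3 gives entry cut-offs, not reference limits.
2. Report by arm the number of patients whose worst post-baseline value moved from normal to abnormal or crossed the entry limit, with the difference in proportions, its exact 95% confidence interval and a listing of those patients. State that this is read descriptively.
3. Keep the tests of change as supportive, label their p-values nominal and unadjusted, and state that a non-significant change is not evidence of laboratory safety.

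**Cost:** analysis wording and a few extra tables from data already collected at each visit; no new patients or measurements. The intervals will be wide at 26 per arm, and the report should say so.

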#### Subgroup analysis

2.10.3

The efficacy of YGJT between subgroups will be evaluated as follows: comparison of the YGJT efficacy for each of the subgroups in the YGJT group with that of the corresponding subgroup in the control group and comparison of the YGJT efficacy among the 3 subgroups of the YGJT group. The statistical significance of any differences between the YGJT group and the control group, among the 3 subgroups, will be analyzed using a generalized linear model with either the Wilcoxson rank sum test or the Kkruskal–Wallis test. All tests will be 2-sided tests, and the significance level will be 0.05.

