#### Subgroup analysis

2.9.4

Participants will be subdivided into the following 3 subgroups: patients who complain of anorexia after surgery, patients who complain of anorexia during radiation therapy or recent radiation therapy, patients who complain of anorexia more than 1 month after chemotherapy. Comparisons of the YGJT group and the control group will also be performed at the subgroup level.

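### One of the two planned subgroup comparisons uses the YGJT arm alone, so it mixes treatment effect with natural course, and no treatment-by-subgroup interaction is named

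*Protocol article*

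**What the plan says.** Protocol article, section 2.9.4, defines three subgroups by treatment context: "patients who complain of anorexia after surgery, patients who complain of anorexia during radiation therapy or recent radiation therapy", and patients whose anorexia is reported more than a month after chemotherapy. It announces one kind of analysis: "Comparisons of the YGJT group and the control group will also be performed at the subgroup level".

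Section 2.10.3 lists two comparisons for judging efficacy between subgroups:

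- **Comparison A**, with controls: "comparison of the YGJT efficacy for each of the subgroups in the YGJT group with that of the corresponding subgroup in the control group".
- **Comparison B**, without controls: "comparison of the YGJT efficacy among the 3 subgroups of the YGJT group".

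On method, it says that differences between the arms and among the three subgroups "will be analyzed using a generalized linear model with either the Wilcoxson rank sum test or the Kkruskal–Wallis test". It adds: "All tests will be 2-sided tests, and the significance level will be 0.05". No treatment-by-subgroup interaction is mentioned.

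**The concern.** Efficacy is a contrast with control. Comparison B has no control, yet the section calls its result efficacy and tests it at the 0.05 level. Mean change in a YGJT subgroup contains the YGJT effect plus whatever would have happened anyway: spontaneous recovery, response to counseling and regression to the mean.

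The subgroup definitions make unequal natural course plausible. Some patients in the radiation subgroup may still be receiving the treatment linked to their anorexia, while the chemotherapy subgroup must be more than a month past theirs.

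The trial is described (section 2.6) as exploratory and meant to inform the design of a later one. A finding that YGJT works better in one setting would be a natural product of this analysis, and comparison B cannot support it. It can also hide a real difference.

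**Working it through.** **Inputs from the protocol article.** Section 2.6: "The sample size was set using an effective size of 0.9", 5% significance, 80% power, 21 evaluable and 26 enrolled per arm. Section 2.10.3: two-sided 0.05 and the Kruskal–Wallis test.

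**Sample size first.** n = (2/0.9²) × (2.0211 + 0.8507)² = 2 × 1.2346 × 8.247 = 20.36, rounded up to 21. Then 21 × 1.2 = 25.2, rounded up to 26. The stated figures reproduce.

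**Assumptions not in the documents.** Equal subgroups: 21/3 = 7 per arm, or 26 split 9/9/8. Normal changes with SD 1. The gaps in natural course are shown as a range.

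**What each contrast estimates.** Let subgroup j have natural course c_j and YGJT effect e_j. Expected change is c_j + e_j on YGJT and c_j on control.

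- Comparison B, subgroups j and k: (c_j + e_j) − (c_k + e_k) = (e_j − e_k) + (c_j − c_k).
- Interaction: [(c_j + e_j) − c_j] − [(c_k + e_k) − c_k] = e_j − e_k.

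Comparison B isolates a difference in effect only if c_j = c_k.

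**False claims of differing efficacy.** Simulated rejection rates with the same effect, 0.9 SD, in all three subgroups, and one subgroup's natural course shifted:

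| Gap in natural course | Within-YGJT Kruskal–Wallis, 7 per cell | Interaction F test |
|---|---|---|
| 0 | about 4% | about 5% |
| 0.5 SD | about 12% | about 5% |
| 0.8 SD | about 24% | about 5% |
| 1.0 SD | about 37% | about 5% |

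With 9/9/8 per arm the within-arm rates are about 4% at no gap, 14% at 0.5 SD and 37% at 0.9 SD. At 0.9 SD with 7 per cell the rate is 31%.

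**Missed differences.** Take true effects of 0/0/0.9 SD offset by natural course of 0.9/0.9/0. All three YGJT means are then equal, and comparison B rejects in only 4–5% of trials. The interaction test rejects in 19–24%.

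**Comparison A.** Two-sample power at 0.9 SD (noncentral t) is 34% with 7 per arm and 42% with 26/3 = 8.67 per arm. If the effect is identical everywhere, the chance that the three tests disagree (one or two of three significant) is 1 − p³ − (1 − p)³:

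- p = 0.341: 1 − 0.040 − 0.286 = 0.67.
- p = 0.419: 1 − 0.074 − 0.196 = 0.73.

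A mixed pattern is thus the usual result with no difference in effect, and cannot be read as evidence of one.

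**Limit of the remedy.** For effects 0/0/0.9 SD and 7 per cell, the mean effect is 0.3 and the interaction noncentrality is 3.5 × (0.3² + 0.3² + 0.6²) = 1.89 on 2 and 36 degrees of freedom. Power is about 20%. Across 7 per cell to 9/9/8 it is about 20–24%.

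**The case against.** The case for the plan has four parts.

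1. *The controlled comparison is there.* A reader might infer that subgroup efficacy is to be judged only inside the YGJT arm. The text does not support that. Section 2.10.3 lists the YGJT-versus-control comparison first, and section 2.9.4 announces only that one. This point stands, and the concern is confined to comparison B and to the missing test of differing effects.

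2. *Comparison B is not purely natural course.* A reader might infer that it measures natural course instead of effect. It measures the sum of the two. With equal natural course it is a valid test, as the 4% rate at zero gap shows. The defect is confounding.

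3. *The generalized linear model could contain an interaction.* The sentence speaks of differences between arms and among subgroups, and the rank tests may be meant as the fallback for non-normal data. Model terms may also sit in a fuller document. This is a fair reading, but not what is written: the rank tests are attached to the model, and neither can test an interaction. Nor would a fuller model justify calling comparison B a comparison of efficacy.

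4. *The size is assumed and the stakes are modest.* No document gives natural-course differences or subgroup sizes. A gap of 0.8–1.0 SD is about as large as the whole planned effect, so the lower rows of the range matter equally. A reader might also infer that the later trial will be steered to the wrong population. No section ties its population to a subgroup p-value, and the Discussion concedes small samples and calls for further studies. The primary analysis is untouched.

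**Conclusion.** The point holds as a limited but definite fault in the written plan. Comparison B is labelled efficacy although it cannot separate effect from natural course. Comparison A does not test whether effects differ, and nothing named in section 2.10.3 does.

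The size depends on a quantity that the documents do not give. There is no inflation if natural course is equal across subgroups, and a false-positive rate of roughly one in eight to over one in three if one subgroup differs by 0.5 to 1.0 SD. These figures assume equal subgroups of 7 per arm, normal changes and a common YGJT effect. That comparison B is confounded does not depend on those assumptions.

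This is a secondary analysis in an exploratory trial. It should be corrected, but it does not threaten the main result.

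**What to change.** In section 2.10.3:

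1. Keep the YGJT-versus-control contrast in each subgroup. Report it as a difference in A/CS change with a 95% CI, from one linear model on all patients with treatment, subgroup, treatment × subgroup and baseline A/CS.
2. Base any claim that efficacy differs between subgroups on the interaction test. Label it exploratory and say that its power is low, so that a non-significant result is not read as equal efficacy.
3. Make the YGJT-arm-only comparison descriptive, with no efficacy interpretation, or delete it.
4. Rewrite the method sentence so that the rank tests are no longer attached to the generalized linear model. If they are kept as a non-normal alternative for the contrasts within subgroups, say so.

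The cost is a change of wording and one model. The control-arm data are already planned, and neither the sample size nor the visits change.
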